### Participants’ Eligibility Criteria

Textbox 1 shows the inclusion, exclusion, and withdrawal criteria.

Inclusion, exclusion, and withdrawal criteria.
**Inclusion criteria**
Participants meeting the following criteria will be included:Chronic insomnia based on established diagnostic criteria (*International Classification of Sleep Disorders, Third Edition*), including a report of sleep initiation or maintenance problems, adequate opportunity and circumstances to sleep, daytime consequences, and duration of at least 3 months, with a frequency of at least 3 times per weekInsomnia Severity Index score between 8 and 21Age between 20 and 55 years and male or female sexHamilton Depression Scale score ≤14No treatments for insomnia, including medication and acupuncture, received during the past monthRight-handednessUnderstanding the process of this study and agreeing to participate and sign the consent form
**Exclusion criteria**
Participants meeting any of the following criteria will be excluded:Severe pain or systemic diseases (endocrine system diseases, motor system diseases, autoimmune diseases, infectious diseases, and metabolic diseases such as diabetes mellitus) that affect sleepHistory of metal, head surgery, and implantation of any metal or other contraindications for functional magnetic resonance imagingInsufficient language skills and mobility to perform Baduanjin qigongMajor depressive disorder, anxiety disorder, panic disorder, or other mental disorders, and alcohol or caffeine addictionPregnancy, breastfeeding, or planning to become pregnant
**Withdrawal criteria**
Participants meeting the following criteria will be excluded after the start of the trial:Occurrence of an adverse event related to the researchParticipant’s personal request

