**Methods:**

A randomized controlled trial will be conducted on 86 patients, who will be divided into a BDJQG group and a cognitive behavioral therapy for insomnia group at a ratio of 1:1. Interventions in both groups will be given to the participants 7 times a week for 8 weeks, and the participants will be followed up for 4 weeks. The primary outcome is the change in the Pittsburgh Sleep Quality Index from baseline to week 8. The secondary outcomes are the changes in the Hyperarousal Scale, Insomnia Severity Index, Fatigue Scale-14, wrist actigraphy, salivary cortisol level, and functional magnetic resonance imaging from baseline to week 8. All main analyses will be carried out on the basis of the intention-to-treat principle.

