### Study Setting

Participants will be recruited from the Shanghai Municipal Hospital of Traditional Chinese Medicine. Eligibility for inclusion will be determined by 2 orthopedic surgeons based on predefined inclusion and exclusion criteria. Participants who are determined to be eligible and provide written informed consent will be randomly allocated to either the BDJQG group or the CBTI group in a 1:1 ratio. The BDJQG group will undergo BDJQG treatment, while the CBTI group will receive cognitive behavioral therapy for insomnia. Both groups will undergo an 8-week-long treatment program, consisting of 1 supervised session per week at Shanghai University of Traditional Chinese Medicine and the remaining 6 days of the week completed at home. The study will span a total of 13 weeks, comprising a 1-week-long screening period, an 8-week-long treatment phase, and a subsequent 4-week-long follow-up period.

Assessments using various scales will be conducted at baseline, the 4-week intervention mark, the 8-week intervention mark, and the 4-week follow-up. SCL will be measured at baseline, the 4-week intervention mark, and the 8-week intervention mark. Actigraphy and fMRI assessments will be administered at baseline and the 8-week intervention mark. Figure 1 gives a visual representation of the research process, and Table 1 shows an overview of the study’s time points.

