### Adverse Events and Assessment of Safety

Adverse events (AEs) encompass any untoward and nonsignificant occurrences, namely abnormal experimental findings, symptoms, or illnesses that transpire during the course of the study, irrespective of their causal relation to the intervention. It is important to note that numerous authors have attested to the relative safety of qigong as an approach to addressing various health conditions, including hypertension, with no records of severe AEs. In the event of any unexpected AEs, categorized as functional abnormalities brought about by the intervention, such as symptoms like headache, dizziness, vertigo, head distension, tinnitus, chest tightness, aggravated shortness of breath, heart palpitations, muscular soreness or pain, profuse cold perspiration, irritability, neurasthenia, hallucinations, paranoia, or psychological stress—regardless of their treatment association—prompt notification will be made to the nearest affiliated Shuguang Hospital physician. The physician will then conduct an assessment and initiate appropriate medical intervention.

In instances where serious AEs are encountered, the investigator will promptly report the incident to the primary investigator and the ethics committee to collectively determine whether the affected participant should be withdrawn from the study and the associated treatment. The investigator will earnestly strive to avert and manage any potential harm that may arise during the course of the study. If, following the assessment by the expert committee, the AE is determined to be linked to the qigong treatment, the research team will assume responsibility for covering the cost of treatment and providing appropriate financial compensation for any damage arising from the trial. This comprehensive approach to describing AEs and ensuring the assessment of safety closely adheres to the framework delineated in the study conducted by Guan et al [27].

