### Ethical Considerations

This study will adhere to the principles outlined in the Declaration of Helsinki, ensuring that no additional harm or risks are imposed on the participants. The study has been meticulously designed in compliance with the Standardized Protocol Items, encompassing the recommendations for interventional trials (SPIRIT [Standard Protocol Items: Recommendations for Interventional Trials]) checklist, and has received approval from the ethics committee of Shanghai Municipal Hospital of Traditional Chinese Medicine (2023SHL-KY-17-01). Furthermore, the study has been duly registered in the Chinese Clinical Trials Registry in 2023 (ChiCTR2300069241). The information presented in this report is derived from protocol version 1.0. Before the commencement of the trial, the participants will undergo a comprehensive orientation session regarding the study protocol and their associated responsibilities. This briefing will encompass a detailed explanation of the required physical examinations and relevant precautions. Of paramount importance, the participants will be unequivocally apprised that their engagement in the study is entirely voluntary, and they retain the prerogative to decline participation or withdraw at any juncture without any impact on their medical care or other associated benefits. Notably, if a participant opts to withdraw from the study, any previously collected data will remain intact and be incorporated into the final analysis. To initiate any study-related interventions, explicit written informed consent will be diligently obtained from each participant. A designated research assistant will be entrusted with the responsibility of securing informed consent from all participants. Separate informed consent forms have been developed for the collection of magnetic resonance imaging and saliva samples. Furthermore, all participants will be asked for their consent for the potential publication of identifying information or images within an internet-based open publication, in accordance with established ethical guidelines. The study data will be anonymous or deidentified. Upon the conclusion of the study, the patients will be extended an invitation to continue their 4-week follow-up period at the Shanghai University of Traditional Chinese Medicine, located in Shanghai, China. The 8-week BDJQG program is an enduring initiative, and the participants will maintain their eligibility to engage in this program. Should they desire to do so, the participants can opt to attend BDJQG or CBTI classes free of charge following the culmination of their participation in the study. As an additional incentive to bolster follow-up participation, the participants will be furnished with a large gift pack that will include specialized topical pain patches, a wellness pot, and ¥300 (US $41.98) at the conclusion of the follow-up evaluation. This provision is aimed at enhancing their enthusiasm for continued participation in the follow-up phase.

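### The withdrawal rule removes anyone with a research-related adverse event, whatever its severity, without separating stopping treatment from leaving assessment, and conflicts with the serious-event procedure

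*Protocol article*

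**What the plan says.** Four places in the protocol article bear on this.

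- **Withdrawal criteria (Textbox 1).** "Participants meeting the following criteria will be excluded after the start of the trial". Two criteria follow: a research-related adverse event, and the participant's own request. No grade or seriousness is attached to the first.
- **Adverse Events and Assessment of Safety.** The definition is wide: "Adverse events (AEs) encompass any untoward and nonsignificant occurrences". It applies regardless of cause, and the symptoms listed include headache and muscle soreness. For unexpected events a physician is notified: "The physician will then conduct an assessment and initiate appropriate medical intervention". Withdrawal is not mentioned there. For serious events, the ethics committee and the primary investigator are informed, and the parties are "to collectively determine whether the affected participant should be withdrawn from the study and the associated treatment". The only judgement of relatedness described comes in the compensation clause: "If, following the assessment by the expert committee, the AE is determined to be linked to the qigong treatment".
- **Abstract (Methods) and Study Setting.** "All main analyses will be carried out on the basis of the intention-to-treat principle". The visit schedule is: "Assessments using various scales will be conducted at baseline, the 4-week intervention mark, the 8-week intervention mark, and the 4-week follow-up". The primary outcome is the change in PSQI from baseline to week 8.
- **Ethical Considerations.** Data are kept in one stated situation: "if a participant opts to withdraw from the study, any previously collected data will remain intact and be incorporated into the final analysis".

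**The concern.** Read literally, mild soreness from qigong practice, once judged related, ends participation. A serious related event, by contrast, falls under two rules that give different answers: automatic exclusion in the textbox and a case-by-case decision in the safety section.

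The statistical problem is the missing outcome. Exclusion happens after randomisation and for a reason connected with treatment. Someone excluded before week 8 has no primary endpoint, although someone excluded after week 4 still has a week-4 score. This loss is avoidable, because a participant who stops practising can still complete a self-report questionnaire. It works against the intention-to-treat commitment, although the rule is not a stated exclusion from the analysis.

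The loss might also differ between arms. The trigger needs a judgement of relatedness, the only one described concerns qigong, and only the statistical analysts are blinded. Uneven triggering is therefore possible, but nothing in the article shows that it will occur.

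**Working it through.** **Comparing the rules by type of event**

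| Event | Withdrawal criteria | Adverse Events section | Result |
|---|---|---|---|
| Related, serious | Excluded | Collective decision on whether to withdraw | Direct conflict |
| Related, not serious | Excluded | Assessment and care; silent on withdrawal | No conflict; exclusion applies even to mild events |
| Unrelated, serious | Not triggered | Collective decision | No conflict |

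The collective decision also treats leaving the study and stopping treatment as one step, so neither route secures later assessments. The retention sentence in Ethical Considerations covers data already collected and names only participants who choose to withdraw.

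**Reproducing the plan's figures (Sample Size)**

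Inputs: difference 1.78, one-sided alpha 0.025, power 0.9, 34 per group, about 20% attrition.

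- Enrolment: 34/0.8 = 42.5, rounded up to 43 per group and 86 in total. This matches.
- Allowance for losses: 43 − 34 = 9 per arm (20.9%).
- The text shown gives no SD, so it is back-solved: SD = √[34 × 1.78² / (2 × (1.960 + 1.282)²)] = 2.264.
- SE of the difference: 2.264 × √(2/34) = 0.549.

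**Illustrating the size of bias**

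The article gives no event rates, so every count and PSQI difference here is an assumption. Let d be how much worse (higher) the week-8 PSQI of excluded participants would have been than that of those remaining, equal in both arms. Other losses are taken as balanced and unrelated to outcome. Then

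bias = (excluded in BDJQG − excluded in CBTI)/43 × d.

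d = 1 is 1/2.264 = 0.44 SD, and d = 2 is 0.88 SD.

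| Excess in BDJQG | d = 1 | d = 2 |
|---|---|---|
| 0 | 0 | 0 |
| 1 | 1/43 × 1 = 0.023 | 1/43 × 2 = 0.047 |
| 2 | 2/43 × 1 = 0.047 | 2/43 × 2 = 0.093 |
| 4 | 4/43 × 1 = 0.093 | 4/43 × 2 = 0.186 |

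These favour BDJQG. The sign reverses if the excess is in CBTI or if those excluded would have slept better. The largest value is 0.186/1.78 = 10.5% of the planned difference.

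**Effect on error rates**

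One-sided type I error = P(Z > 1.96 ∓ bias/SE). Power = P(Z > 1.96 − (1.78 ± bias)/0.549).

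| Largest bias | Bias/SE | Type I error (nominal 2.5%) | Power (nominal 90%) |
|---|---|---|---|
| ±0.093 (excess 2, d = 2) | 0.17 | 1.7% to 3.7% | 86.7% to 92.7% |
| ±0.186 (excess 4, d = 2) | 0.34 | 1.1% to 5.2% | 82.7% to 94.7% |

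Even 4 exclusions in one arm use 4 of the 9 losses already allowed (44%), so no further loss of power from reduced numbers is claimed.

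**The case against.** The strongest reply is that this is a condensed article. The criteria are two short items in a textbox taken from a protocol version that is not shown, where grading and follow-up after withdrawal would commonly be set out. That would answer a complaint about missing detail. It does not answer this one, because the article states a mandatory rule and a second rule that disagrees with it.

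The two might be reconciled by treating the collective decision as the process through which the withdrawal criterion is applied. That reading is possible for judging relatedness. But once a serious event is judged related, one text excludes and the other still asks whether to withdraw. It is fair that this case should be rare: the safety section says no severe events are on record with qigong.

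Several other points stand. The trigger refers to the research as a whole and is neutral between arms, and the qigong-specific sentence concerns compensation, so arm imbalance is only a possibility. The bias figures rest on assumed counts and differences and span both signs. The losses may already sit within the attrition allowance. Withdrawing participants from treatment after a related event is a defensible safety choice. None of this justifies ending assessment as well, and neither intention to treat nor retention of earlier data can recover a week-8 score that was never collected.

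**Conclusion.** The concern holds, as a minor one. The textbox rule is mandatory, unrestricted by severity, and covers treatment and assessment together. It directly contradicts the safety section only for related serious events. Followed as written, it creates avoidable missing week-8 PSQI values for a post-randomisation reason that may differ by arm.

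The effect is probably small. An excess of 1 or 2 exclusions in one arm shifts the estimate by 0.02 to 0.09 point, and an excess of 4 by at most 0.19, in either direction. These figures rest on assumed exclusion counts, an assumed difference of 1 or 2 PSQI points, and an SD back-solved from the stated sample size. The bias is zero if both arms lose equal shares of similar participants.

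**What to change.** Amend the Withdrawal criteria so that a related adverse event, or a request to stop, ends at most the assigned intervention. For an adverse event, that decision should be clinical and follow the process in Adverse Events and Assessment of Safety, which removes the conflict. State that the week 4, 8 and 12 assessments still due will continue unless the participant withdraws consent to them. Extend the data-retention sentence in Ethical Considerations to withdrawals made by the study team. For anyone already excluded, report the arm, timing and reason.

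The cost is a short amendment and follow-up contact with a few participants. The right to leave the trial entirely is unchanged. All 86 participants were enrolled at submission, with data collection due to end in January 2024. The change therefore helps only those with assessments still due and cannot recover week-8 values already missed; the reporting step remains possible in any case.

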### Interventions

The two arms of the trial are (1) the intervention arm (BDJQG) and (2) the control arm (CBTI).

#### Intervention Arm (BDJQG Group)

BDJQG consists of 8 forms, which are shown in Multimedia Appendix 1. A qigong teacher from Shanghai University of Traditional Chinese Medicine, who has been involved in qigong education for at least 5 years, will be in charge of the concentrated supervision of the exercise and correction of the exercise posture for 1 hour every Sunday throughout the intervention period. The teacher will first lead a 5-minute stretching and relaxation exercise session to be done before the qigong exercise; and they will then introduce and demonstrate each movement, explain precautions, and answer the participants’ questions for 5 minutes. Then, the teacher will give individual guidance to each participant by correcting their movements. This will last for 30 minutes. Finally, all participants will be told to practice qigong together for 20 minutes. The participants will be asked to practice at home for 30 minutes on the remaining 6 days of the week, to practice on WeChat (Tencent) cluster video at 6 PM daily, and to practice under video supervision. Private video surveillance will be carried out if this is deemed appropriate by an individual participant. A “practice log” will be distributed, to be filled in after each exercise. The entire treatment will last for 8 weeks. The BDJQG intervention will be in line with the descriptions provided in the study by Xie et al [25].

#### Control Arm (CBTI Group)

The CBTI protocols used in this study are based on the comprehensive guide titled *Cognitive Behavioral Treatment of Insomnia: A Session-by-Session Guide* [26]. The participants assigned to the CBTI group will undergo an 8-week-long cognitive behavioral therapy program for insomnia, guided by an experienced psychotherapist, with each session spanning 1 hour and occurring weekly. Additionally, the participants will be provided with a “practice log” to document their activities and progress after each video session.

### Follow-Up Period

An 8-week-long follow-up will be conducted subsequent to the conclusion of the trial, during which the participants will resume their regular lifestyles. However, it is imperative that all of the participants maintain a record of their daily exercise or study activities. To facilitate this, WeChat will be used as a platform for the participants to periodically capture and share photos, providing the researchers with a comprehensive account of their daily exercise or study routines. Upon the culmination of the follow-up period, a reassessment of several metrics, including the Pittsburgh Sleep Quality Index (PSQI), Insomnia Severity Index (ISI), HAS, and Fatigue Scale-14 (FS-14), will be conducted. The objective of this follow-up assessment is to evaluate the enduring or long-term effects of BDJQG on individuals with insomnia, as elucidated in a study conducted by Guan et al [27].

### Quality Control

The specific movements and the corresponding intensity levels used in the BDJQG regimen will be meticulously tailored to individual prescriptions, with variations designed to minimize disparities. Preceding the commencement of the experimental phase, each participant will undergo a structured training program spanning 3 days, administered by a traditional Chinese medicine practitioner with a minimum of 5 years of clinical experience. This training regimen is intended to impart standardized BDJQG movements to ensure uniformity and precision among the participants.

### Outcomes

#### Primary Outcome (PSQI)

The primary outcome is the change in PSQI from baseline to week 8. The PSQI is a comprehensive self-report instrument comprising 19 items aimed at evaluating sleep quality and disturbances experienced within a 1-month time frame. These items collectively contribute to the generation of 7 distinct “component” scores, encompassing assessments of subjective sleep quality, sleep latency, sleep duration, habitual sleep efficiency, sleep disturbances, use of sleeping medication, and daytime dysfunction. The sum of the scores derived from these 7 components yields a singular global score. The total global score spans a range from 0 to 21, with a lower global score indicative of a higher quality of sleep [28].

#### Secondary Outcomes

The secondary outcomes include the changes in ISI, HAS, FS-14, actigraphy, SCL, and fMRI from baseline to week 8.

##### ISI Instrument

The ISI is a self-report instrument encompassing 7 items intended to assess various aspects of insomnia, including the challenges associated with falling asleep and maintaining sleep, overall sleep satisfaction, daytime functioning, impaired attention attributable to sleep disturbances, the degree of distress caused by insomnia-related symptoms, and the level of preoccupation with insomnia-related concerns. Each of these aspects is evaluated on a 5-point scale. The cumulative ISI score ranges from 0 to 28 points and is categorized as follows: 0-7=absence of insomnia; 8-14=mild insomnia; 15-21=moderate insomnia; and 22-28=severe insomnia [29].

##### HAS Instrument

The HAS comprises 26 self-report items designed to gauge a range of cognitive and behavioral factors associated with heightened information processing, propensity for introspection, tendencies to engage in deep emotional reflection, and heightened responsiveness to unforeseen stimuli, all of which are postulated to be indicative of cortical arousal [30]. Elevated scores on this scale are suggestive of an increased state of arousal. Consequently, the HAS serves as a valuable tool for assessing the effect of interventions on cognitive and somatic hyperarousal levels [31].

##### FS-14 Instrument

Fatigue is a prominent consequence of CI, as consistently documented in previous research studies [32,33]. The FS-14 is a self-report assessment tool comprising 14 items designed to capture both physical and mental aspects of fatigue. On this scale, a higher score is indicative of a more pronounced and debilitating level of fatigue.

##### Actigraphy

The ActiGraph GT9X Link (Actigraphy LLC) will be worn on the participants’ wrists to record sleep quality by noting sleep awakenings, total sleep time, sleep onset, sleep latency, and efficiency of sleep. Subsequent analysis of sleep conditions and sleep quality will be executed using the ActiLife6 software (version 6.8.1; Actigraphy LLC) [34]. The participants will be instructed to wear the device continuously for 3 consecutive days, both before and after the 8-week-long intervention period.

